**Table 4: Study measures collected at each time point**

| Study Measure                                                        | Time point |    |    |    |     |    |
|----------------------------------------------------------------------|------------|----|----|----|-----|----|
|                                                                      | Enrol      | 6w | 6m | 1y | 18m | 2y |
| Demographics                                                         | X          | X  | X  | X  | X   | X  |
| Contact details                                                      | X          | X  | X  | X  | X   | X  |
| PRIMARY OUTCOMES                                                     |            |    |    |    |     |    |
| Maternal                                                      |            |    |    |    |     |    |
| Parent care: Nutrition, Safety, Sleep                                |            |    |    | X  |     | X  |
| Parent responsivity                                                  |            |    |    | X  |     | X  |
| Home Environment:                                                    |            |    |    |    |     |    |
| Confusion, Hubbub and Order scale (CHAOS)                            | X          |    |    | X  |     | X  |
| Home Observation for Measurement of the Environment (HOME) subscales |            |    |    | X  |     | X  |
| MacArthur Communicative Development Inventory (MCDI)                 |            |    |    |    |     | X  |
| SECONDARY OUTCOMES                                                   |            |    |    |    |     |    |
| Maternal                                                      |            |    |    |    |     |    |
| Pregnancy Outcomes                                                   |            | X  |    |    |     |    |
| Social support                                                       | X          |    |    | X  |     | X  |
| Quality of Life                                                      | X          | X  |    | X  |     | X  |
| Maternal mental health                                               | X          | X  |    | X  |     | X  |
| Parenting Wellbeing                                                  | X          |    |    | X  |     | X  |
| General Health Questionnaire                                         | X          | X  | X  | X  | X   | X  |
| Parenting self-efficacy                                              | X          |    |    | X  |     | X  |
| Health service use                                                   |            | X  | X  | X  | X   | X  |
| Health literacy                                                      |            |    | X  |    | X   |    |
| Parenting styles                                                     | X          |    |    | X  |     | X  |
| Child                                                         |            |    |    |    |     |    |
| Mental and general health                                            |            |    |    |    |     | X  |
| General Health                                                       |            | X  | X  | X  | X   | X  |
| Sibling                                                       |            |    |    |    |     |    |

| Study Measure                                           | Time point |    |    |    |     |    |
|---------------------------------------------------------|------------|----|----|----|-----|----|
|                                                         | Enrol      | 6w | 6m | 1y | 18m | 2y |
| Mental health/behaviour                                 | X          |    |    | X  |     | X  |
| Nurse                                            |            |    |    |    |     |    |
| Use and knowledge of evidence-based clinical strategies | X          | X  | X  | X  | X   | X  |
| MONITORING VARIABLES                                    |            |    |    |    |     |    |
| Maternal social capital/sensitive issues                | X          |    |    | X  |     | X  |
| Child birth data                                        |            | X  |    |    |     |    |
| Child growth data (e.g. height & weight)                |            | X  | X  | X  | X   | X  |
| Intervention dose and fidelity                          |            | X  | X  | X  | X   | X  |

Time points: w=week, m=month, y=year. Enrolment will occur within a fortnight of screening at the antenatal hospital clinic. Monitoring items are variables that may be used to describe the sample or to control for potential confounding and are not collected as demographics.

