**Table 2: Primary and Secondary Outcome Measures**

| Measure                                                           | Description                                                                                                                                                                   |
|-------------------------------------------------------------------|-------------------------------------------------------------------------------------------------------------------------------------------------------------------------------|
| Demographics                                                      | E.g. psychosocial and socioeconomic risk factors collected via self report                                                                                                    |
| Contact details                                                   | Family and alternate contact details                                                                                                                                          |
| PRIMARY OUTCOMES                                                  |                                                                                                                                                                               |
| 1. Parent care:                                                   |                                                                                                                                                                               |
| Nutrition : child height and weight, mealtime diary report | Child height and weight collected via direct observation; study-designed diary based on LSAC diary measuring types of food consumed in 24-hours, collected via parent report. |
| Safety : Home safety audit                                 | Observational safety check to identify household hazards, adapted from the Safe Place Project intervention.                                                                   |
| Sleep : Sleep problems                                     | Single parent report item drawn from LSAC: "How much of a problem is your child's sleep", responses "none", "mild", "moderate", and "large".                                  |

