#### **6.4 Blinding Arrangements**

The project manager, participants and nurses will be aware of the allocation to treatment arm to enable organisation for the mothers to receive the active or control intervention. Research staff responsible for conducting outcome assessments will be blinded to treatment allocation. Families will be asked not to disclose their randomisation status at assessments; however, those that do will be recorded in the study database and this 'unbinding' will be examined as a potential confounding variable in the outcome analyses.

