## **7. STUDY VISITS AND PROCEDURES SCHEDULE**

The Study diagram in Section 4.2 and Figure 3 below depict the study visits schedule. From April 2013 to March 2014, researchers will approach women at antenatal clinics listed in Section 1.1 to invite women to take part in the screening survey (**Appendix 15**). At this point, consent involves agreeing to complete the screening survey and, if eligible, being invited into the right@home trial. Researchers will then visit interested and eligible women in their homes within 1-2 weeks of the initial screening procedure, to tell them more about the right@home study, and collect informed consent for participation in the randomised controlled trial and a thorough baseline assessment.

Once women complete the baseline assessment, they will be randomised into one of the intervention or usual care arms. Whether this randomisation takes place in the woman's home (at the end of the enrolment visit) or over the phone will depend on whether the intended electronic data collection processes can incorporate the web-based randomisation program, and whether the tablets can connect via 3G/wireless internet. Once a woman is randomised, her details will be sent to the right@home nurse coordinator responsible for that region, and the nurse will be responsible for initiating contact and beginning the intervention. Follow-up assessments will be conducted by the research team via phone at 6 weeks, 6 months and 18 months postpartum, and via face-to-face home visits at 12 and (the final follow-up at) 24 months.

Due to the anticipated low literacy level of the participant group, we are designing all assessments so that they can be completed face-to-face by interview. Responses will be recorded by researchers electronically on tablets, except for some sensitive questions (highlighted in the questionnaire), where the participant will be given the option to complete by themselves either by reading it or having it read to them.

**Figure 5: Graphical depiction ('Perera diagram') of the components of the trial shared and unique to the intervention and control groups**

| Time point relative to randomisation                | Intervention                                                                                                             | Control |

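### Sections 6.4 and 7 (Table 4) allow variables that arise after randomisation to be treated as confounders; adjustment should be limited to pre-randomisation variables plus child sex

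*Protocol*

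**What the plan says.** **Timing of randomisation.** Section 7 states: "Once women complete the baseline assessment, they will be randomised into one of the intervention or usual care arms". This happens during pregnancy, and Section 5.1.1 has programme visits starting antenatally.

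**Monitoring variables.** Table 4 has four rows under this label. "Maternal social capital/sensitive issues" is collected at enrolment, 1 year and 2 years. "Child birth data" is collected at 6 weeks only. Child growth and "Intervention dose and fidelity" are each collected from 6 weeks to 2 years, with no enrolment value. The footnote gives the permitted uses: "Monitoring items are variables that may be used to describe the sample or to control for potential confounding". It does not say which row serves which use.

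**Disclosure.** Section 6.4 asks families not to reveal their arm at assessments, has any disclosure recorded, and says that it "will be examined as a potential confounding variable in the outcome analyses".

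**Other roles of the same variables.** Table 2 lists "child height and weight, mealtime diary report" under the primary outcome Parent care (Nutrition). It lists dose and fidelity under the secondary Nurse outcomes, recorded from nurses' home visits.

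**Analysis sections.** Section 10.2 promises an intention-to-treat comparison whatever the mothers' compliance. Section 10.3 gives the covariates chosen in advance for the regression models: child gender, socio-demographic characteristics, and maternal health, mental health and self-efficacy.

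**The concern.** A confounder of a treatment comparison must influence allocation or share a cause with it. Allocation here is random, so nothing that arises afterwards can do either. Such variables can be consequences of allocation, and conditioning on a consequence changes what the arm coefficient estimates.

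- **Dose and fidelity** measure receipt of the programme. Section 5.2 measures compliance with the fidelity instruments, so adjusting for them adjusts for compliance, which Section 10.2 says the comparison disregards.
- **Child growth** may respond to a programme with a nutrition module, and it is itself a primary measure. The same height and weight cannot be both an outcome of the comparison and a confounder of it.
- **Child birth data** follow antenatal visits and so may also be affected.
- **Disclosure** is made by mothers who know their arm. It may differ between arms and may be related to engagement or prognosis.

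At stake is how an adjusted result would be read. The protocol as worded would permit an analyst to fit such a model and report a reduced or null coefficient as the effect with confounding removed. The trial is sized for 80% power at 0.315 SD, which leaves little room for attenuation.

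**Working it through.** **1. The plan's own figure (Section 10.1).** Inputs: difference 0.315 SD, power 80%, ICC 0.02, cluster size 29, retention 60%. Two-sided alpha of 0.05 is assumed, as the protocol states none.

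- Per arm before inflation: 2 × [(1.960 + 0.842)/0.315]² = 158.2
- Design effect: 1 + (29 − 1) × 0.02 = 1.56, giving 158.2 × 1.56 = 246.8
- After attrition: 246.8/0.60 = 411

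The stated 400 is reproduced to within 3%. With 400 × 0.60 = 240 retained per arm, power is 78.9%. The present point does not depend on this figure. It supplies only the effect size and the retained numbers used below.

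**2. Timing of each variable (Table 4 and Section 6.4)**

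| Variable | Value before randomisation? | Other role |
|---|---|---|
| Maternal social capital/sensitive issues | Yes (enrolment); also 1 and 2 years | none listed |
| Child birth data | No (6 weeks) | none listed |
| Child growth | No (6 weeks to 2 years) | primary measure (Nutrition) |
| Dose and fidelity | No (6 weeks to 2 years) | secondary (Nurse) outcome |
| Disclosure to assessor | No | none listed |

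Only the enrolment value in the first row is a proper adjustment variable.

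**3. Dose: collinearity with arm.** Dose is 0 in controls. In the programme arm take a mean of 25 visits (the planned minimum in Section 5.1.2, used here as an assumed mean) and an assumed SD s. With 1:1 allocation:

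- Between-arm variance of dose: 0.25 × 25² = 156.25
- Total variance: 156.25 + 0.5s²
- r² = 156.25/(156.25 + 0.5s²); SE multiplier = √[1/(1 − r²)]

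| s | r | Variance inflation | SE multiplier |
|---|---|---|---|
| 4 | 0.975 | 20.5 | 4.5 |
| 5 | 0.962 | 13.5 | 3.7 |
| 8 | 0.911 | 5.9 | 2.4 |
| 10 | 0.870 | 4.1 | 2.0 |

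A yes/no dose variable is identical to arm, so that model cannot be fitted.

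**4. Dose: the estimate.** Simulation with 1,000 runs, 240 per arm, no clustering, visit SD 6, and an effect proportional to visits averaging 0.315 SD:

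- Without dose: estimate 0.317, SE 0.091, rejection rate 92%
- With dose: estimate 0.011, SE 0.285, rejection rate 5%

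If the effect does not depend on the number of visits, the estimate stays near 0.315 but the SE does not recover. Power is then about Φ(0.315/0.285 − 1.96) = Φ(−0.855), or about 20%.

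**5. Growth.** Assume a 0.2 SD arm effect on growth and a within-arm correlation of 0.25 with the outcome through a shared cause. The adjusted coefficient is 0.315 − 0.25 × 0.2 = 0.265. Simulation gave 0.261, with a rejection rate of 83%. If growth instead carried half of a 0.30 SD effect, the adjusted estimate would be about 0.15.

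**6. Disclosure.** Assume disclosure by about 10% of controls and 35% of programme mothers, likelier among programme mothers with better prognosis. The adjusted estimate is 0.26 (simulated 0.255, rejection rate 78%). Reversing the link, so that those with worse prognosis disclose more, gives 0.37. With no link to prognosis, the estimate stays at about 0.315.

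**The case against.** The strongest reply is that no such model is planned. The Table 4 footnote is permissive and offers description as an alternative use, which is the natural reading for dose. Section 6.4 promises only to examine disclosure. Section 10.3, which governs the models, lists its covariates and includes none of these variables, and Section 10.2 commits to intention to treat. Final covariate sets and the handling of unblinding also commonly belong in a statistical analysis plan, which is not shown.

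Much of this stands. A reader might infer that these variables are going to be used as confounders and that the primary result will therefore be biased. The documents do not support that. They allow adjustment for the Table 4 items without requiring it, and they do not place any of them in the main model. Nor are all monitoring items unsuitable: the enrolment value of maternal social capital is a legitimate covariate and gives the footnote's wording one proper use. The growth and disclosure figures rest on assumed inputs with no source in the protocol. Checking whether known disclosure alters the results is also a reasonable sensitivity question; calling it confounding is what is wrong.

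The reply does not remove the point. Both sentences are stated rules rather than gaps left for a later document. Section 6.4 places disclosure in the outcome analyses themselves, and the footnote licenses adjustment for three items that have no pre-randomisation value, one of which is also a primary measure.

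**Conclusion.** The point holds as a fault in stated wording. Sections 6.4 and 7 classify post-randomisation variables as potential confounders, which they cannot be in a randomised comparison. Acting on that wording would conflict with Section 10.2, and the double role of child height and weight is an internal inconsistency. It is not shown that the main analysis in Section 10.3 is affected.

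The size depends on use. For dose, near-collinearity follows from the design: the SE rises 2.4- to 3.7-fold for visit SDs of 8 to 5 around an assumed mean of 25. Loss of the estimate itself additionally requires that the effect act through the number of visits. For growth, the examples give 0.26 from 0.315, or 0.15 from 0.30. For disclosure they range from 0.26 to 0.37 around 0.315, so even the direction is not fixed. These are illustrations of a risk, not estimates of a bias in this trial.

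**What to change.** Three wording changes:

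1. **Section 10.3:** state that outcome models adjust only for variables measured before randomisation, including the enrolment value of maternal social capital/sensitive issues, plus child sex.
2. **Table 4 footnote:** state that monitoring items collected after baseline (dose and fidelity, growth, birth data, later social capital values) are descriptive, or are used only in separately labelled compliance or mediation analyses. Keep child growth as an outcome.
3. **Section 6.4:** replace the confounding wording with a statement that disclosure is tabulated by arm and visit and is examined only in a labelled sensitivity analysis, not as a confounder in the main outcome models.

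A complier-average analysis with randomisation as the instrument is optional, if a question about dose is wanted. Setting assessor-rated beside parent-reported measures would not isolate assessor bias, since parents know their allocation.

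The cost is a few sentences of protocol text. Data collection and sample size do not change.

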## 8. CLINICAL ASSESSMENTS

We plan to collect all assessment data electronically via tablets; however, we will print paper versions of all assessments as backup for possible electronic malfunctions.

**Screening:** The purpose of this face-to-face assessment is to identify eligible women and invite them into the right@home trial. As described in Section 6.1, researchers will approach pregnant women in antenatal clinic waiting rooms using the script in **Appendix 16**. Interested women will be asked to complete informed consent (see **Appendix 17**) and complete the screening survey (see **Appendix 15**), either with the researcher or alone. Using the eligibility algorithm identified by the pilot (RCH HREC # 32271, Northern Health HREC P 20/12), researchers will identify eligible women from their survey responses and invite them into the next phase of the trial. This involves describing RCT participation, giving women the information statement for participation in the randomised controlled trial (**Appendix 2**), recording their contact details and organising a time to visit them in their home to conduct the formal enrolment.

**Baseline enrolment:** The purpose of this face-to-face assessment is to formally enrol (i.e. obtain informed consent) for participation in the right@home trial, and conduct a comprehensive baseline assessment of women. A researcher will visit the participant in her home (or at The Royal Children's Hospital or a mutually-convenient location nearby, depending on the woman's preference and researcher safety). The researcher will answer any questions the woman has about the Information Statement given to her at the screening assessment and collect informed consent (see **Appendix 17**). The researcher will then conduct the baseline questionnaire with the mother (see **Appendix 20**). The questionnaire will be collected in a private space, i.e. a separate room with only the mother, the researcher, and any young children that the mother needs to care for, present. The baseline assessment includes the mother completing the SDQ for any children aged 3-6 years (see Sections 4.5 and 7 above). We expect the baseline enrolment assessment will take 50-60 minutes to

complete face-to-face, based on purposeful piloting (i.e. the interviewing was undertaken with the understanding that it would be a slower process than anticipated) with our research staff.

Once the woman completes the baseline assessment, she will be randomised into one of the intervention or usual care arms. Once randomised, the participant's details will be emailed to the right@home nurse responsible for the region, and the nurse will be responsible for initiating contact and beginning the intervention.

## 9. ADVERSE EVENT REPORTING

### 9.1 Definitions

**Adverse Event (AE):** Any untoward medical occurrence in a participant enrolled into this study regardless of its causal relationship to study treatment. Adverse events are classified as serious or non-serious.

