#### **6.6.2 Handling of withdrawals and losses to follow-up**

If the participant is withdrawing from the intervention, the research team will ask whether they are still happy to take part in the research assessments in an effort to maintain the intention-to-treat analysis. If the participant withdraws fully from the study, they will cease to undergo scheduled assessments. Participants will be asked (only if willing) to share the reason for ceasing the intervention or participation in the full trial. Reasons will be recorded by the research team in the study database. Where it is not possible to contact a family, a limited number of follow-up processes will be conducted, including:

- (1) 2 documented phone calls including alternative assessment settings offered,
- (2) 2 documented emails (where email address are provided),
- (3) Contacting Centrelink for updated contact details where consent to record the family's Centrelink is obtained. We are currently making inquiries into whether this is possible and will only be able to do it with the correct authority.

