## **9.2 Assessment and Documentation of Adverse Events**

For the purposes of this study the investigator is responsible for recording all Adverse Events, regardless of their relationship to the study intervention, with the following exceptions:

- Conditions that are present at screening and do not deteriorate will not be considered adverse events.

The description of each AE on the study database will include:

- A description of the AE;
- The onset date, duration, date of resolution;
- Severity (mild, moderate or severe);
- Seriousness (i.e. is it an SAE?);
- Any action taken, (e.g. treatment, follow-up tests);
- The outcome (recovery, death, continuing, worsening);
- The likelihood of the relationship of the AE to the study treatment (Unrelated, Possible, Probable, Definite).

The seriousness of an AE will be assessed by an investigator according to the definition in section 9.1, with the following exception:

- Hospitalisation due to progression of disease will not be considered an SAE for the purposes of this study.

For the right@home study, the most likely AEs/SAEs that nurses and researchers will encounter are psychosocial, substance abuse, home safety and child protection issues (e.g. abuse, neglect). Where an incident that requires a child protection notification occurs during a nurse visit, the nurses will respond in accordance with their local mandatory reporter guidelines. This is part of usual care, and thus involves no change in practice for the nurses. The baseline PIS&C (Appendix 2) includes the following: “We can disclose the information only with your permission, unless required by law”, which alerts the participant to the need to remain within the law.

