### **9.3 Eliciting Adverse Event Information**

Adverse events will be recorded from the time the patient signs the informed consent form until 30 days after the last intervention nurse visit. At every study visit patients will be asked “How have you felt since your last visit?” in order to elicit any medically related changes in their well-being. They will also be asked if they have been hospitalised, had any accidents, used any new medication or changed concomitant medication regimens. In addition, AEs will be documented from physical examination findings, clinically significant lab results or other documents (including patient diaries and correspondence from their primary care physician) that are relevant to patient safety.

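### Section 9.3 ends adverse-event recording on an intervention nurse visit, so control mothers have no end date and intervention mothers who stop visits leave recording while still in the trial

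*Protocol*

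**What the plan says.** Three parts of Section 9 of the protocol set the AE rules.

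- **Definition.** Section 9.1 defines an AE as "Any untoward medical occurrence in a participant enrolled into this study regardless of its causal relationship to study treatment". A serious AE must first be an AE.
- **Expected events.** Section 9.2 makes the investigator responsible for recording all AEs, whatever their cause. It says that for this study "the most likely AEs/SAEs that nurses and researchers will encounter are psychosocial, substance abuse, home safety and child protection issues". It also says: "The seriousness of an AE will be assessed by an investigator according to the definition in section 9.1".
- **Recording period and prompts.** Section 9.3 opens recording when the woman signs consent and closes it "30 days after the last intervention nurse visit". At every study visit she is asked "How have you felt since your last visit", which is done "in order to elicit any medically related changes in their well-being". She is also asked about hospital stays, accidents and medication.

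Other sections settle who has such visits. Under Section 5.1.1 the intervention arm has at least 25 visits from a programme nurse, while the control arm is seen by the regular child and family nursing service. Section 6.8 stops the programme at the child's second birthday. For a mother who leaves the programme, Section 6.6.2 says that "the research team will ask whether they are still happy to take part in the research assessments", so as to preserve the intention-to-treat analysis. Section 7 schedules research contacts in both arms at 6 weeks, 6, 12, 18 and 24 months.

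**The concern.** An AE recording period should start and stop at events that both arms share. This one stops at an event that only one arm can have, and in that arm it depends on how long a mother keeps attending.

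Two consequences follow. Nobody can say from the text when AE recording ends for a control mother. And a mother who gives up the programme but accepts the invitation to stay in the assessments passes out of the recording period, although women who abandon a home-visiting programme are among those whose safety the team would want to follow. If AEs are ever described by arm, the counts would rest on unequal periods.

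A smaller matter is the wording of the definition. Section 9.1 speaks of medical occurrences, while several of the events that Section 9.2 expects most often, such as neglect or a home hazard without injury, are not medical in any ordinary sense.

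**Working it through.** **Control arm.** Section 9.3 needs a last intervention nurse visit. Section 5.1.1 gives control mothers none, and no other section supplies a substitute end date. The rule is therefore undefined for 400 of 800 women (Number of Subjects, Section 4).

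**Intervention arm.** Inputs: 30 days after the last visit (Section 9.3), and research contacts at 6 weeks, 6, 12, 18 and 24 months (Section 7). Taking a month as 30.4 days, 30 days is 30/30.4 = 1.0 month. If the last visit is at child age L months, recording closes at L + 1.0, and the time left to the 2-year assessment is 24 − (L + 1.0), or zero if negative.

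| Last visit (months) | Recording closes (months) | Research contacts after closure | Months from closure to 24 |
|---|---|---|---|
| 3 | 4 | 4 of 5 | 20 |
| 6 | 7 | 3 of 5 | 17 |
| 12 | 13 | 2 of 5 | 11 |
| 18 | 19 | 1 of 5 | 5 |
| 24 | 25 | 0 of 5 | 0 |

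The table shows what the end-date sentence does when read alone. The same section asks the AE question at every study visit, with no exception for mothers who have left the programme. For early stoppers the two sentences conflict: the question is put, but the recording period has formally closed.

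**When is a visit the last one?** Section 5.1.1 schedules visits every two months from 6 months to 2 years, so routine gaps already exceed 30 days. Whether a given visit was the last is known only afterwards, and staff cannot apply the rule as they go. Section 5.2 defines significant non-compliance as 6 months without attendance. A mother so classed has been outside the period for 6 − 1.0 = 5 months only if she never returns. If she resumes, the earlier visit was not her last and she never left the period.

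**Scale.** The protocol does not say how many mothers will stop visits for good yet stay in assessments. As an assumption only, take 5% to 20% of 400, all stopping at 12 months. That is 20 to 80 mothers and 20 × 11 = 220 to 80 × 11 = 880 mother-months formally outside recording, out of 400 × 24 = 9,600, or 2.3% to 9.2%. These are months outside the stated period. They are not missed events, and without event rates they cannot be turned into any.

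**The case against.** **Nothing need be lost.** The AE question continues at every study visit, and research follow-up runs to 24 months in both arms, including for mothers who have left the programme. This stands. A reader might infer from the table that events at the later contacts are certain to go unrecorded. The text supports only a contradiction between two sentences of Section 9.3.

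**Controls are not harmed by an open end.** This also stands. A missing end date loses no control-arm events, and the last scheduled contact is at 24 months anyway. The defect there is an undefined period, which matters when periods are compared.

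**The definition is a drafting mismatch.** A reader might infer that Section 9.1 shuts out the very events Section 9.2 expects. The documents do not support that. Section 9.2 speaks specifically of this study, calls those events AEs or serious AEs, and gives handling steps for them. Some, such as injuries and substance abuse, can be medical in any case. What remains is wording to align.

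**Other data cover the same ground.** In both arms Section 9.1 plans a question about harm from the study at 6 weeks, 6 and 18 months. Table 4 adds health service use at all five follow-ups, maternal mental health at 6 weeks, 1 and 2 years, and home safety and sensitive issues at 1 and 2 years. That lessens the worry, but none of these is stated to feed the AE record. Appendices 21 and 23 are not available here and may add operational steps.

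**The end point could be meant trial-wide.** The period opens at each woman's own signature, so a trial-wide close is not the natural reading. If it is intended, the text should say so.

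**Conclusion.** The point holds as a defect in the stated recording period. Control mothers, 400 of 800, have no defined end, and intervention mothers who stop visits permanently but remain in assessments fall formally outside AE recording while still enrolled. A last visit at 12 months puts the 18- and 24-month contacts outside the period, against the instruction to ask at every study visit.

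The consequence is confined to safety oversight of early stoppers and to any description of AEs by arm; the protocol states no formal AE comparison. The sample size and the efficacy analysis are unaffected. A reader might go on to infer a bias in AE counts of known direction, because nurses pass some intervention-arm events to the team (Sections 6.2.2 and 6.6.1). The size and direction are unknown, and nurses have no stated duty to enter AEs.

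The conclusion assumes that the end date applies mother by mother and that no appendix overrides it. Severity is minor to moderate.

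**What to change.** In Section 9.3, end AE recording at one point common to both arms: the 2-year assessment, or full withdrawal from the study if earlier. This can give up as much as 30 days of recording after a visit close to the second birthday. If those days matter, use a calendar rule that applies equally to controls, such as 30 days after the child's second birthday. State that the existing prompts are put at all research contacts, by phone or face to face, in both arms, whether or not the mother still receives visits. No new interview items are needed.

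As a secondary change, extend the AE definition in Section 9.1 to new or worsened psychosocial, substance abuse, home-safety and child-protection events. Keep the Section 9.2 exception, "Conditions that are present at screening and do not deteriorate will not be considered adverse events", which limits the extra recording in a group selected for existing difficulties. The seriousness criteria can stay, so a child-protection event with none of the listed outcomes would be a non-serious AE. In any AE summary by arm, list nurse-detected events separately, because only one arm has programme nurses to detect them.

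The cost is an amendment to two sections, with ethics approval under Section 12.3, and somewhat more events to record. Each AE needs dates, severity, action, outcome and relationship to treatment, and follow-up to resolution where possible.
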